### Standard Care

2.8

In the pre‐intervention phase, we will observe the conventional wound care and documentation practices for PI and IAD in the selected wards. These practices are governed by internal hospital standard operating procedures for wound care and documentation, developed in accordance with the German national expert standards “Pressure Ulcer Prevention in Nursing” and “Nursing Care for Patients with Chronic Wounds” (Büscher et al. 2021; Schiemann 2009). These guidelines are available to nurses through a digital platform within the hospital. For electronic documentation of wounds, nurses capture wound images using a digital camera and upload these images to the computer‐based clinical documentation system, where they also enter additional details about the wound characteristics. No changes to the hospital infrastructure or processes related to wound care and documentation are anticipated during the study period.

### Intervention

2.9

In the intervention phase, nurses will use the AI‐based application developed in the KIADEKU technical sub‐study (German Clinical Trials Register number DRKS00029961) on tablets and smartphones to provide wound care and documentation. The final version of the AI model is still under development and will be specified upon the publication of results. The AI‐based application used is a prototype demonstrator and has not been approved as a medical device. Therefore, this study is not a clinical evaluation under the Medical Device Regulation but a pilot and feasibility study to explore the potential of AI in nursing and support further development.

Before the intervention, nurses in the intervention group will receive training on how AI works, the relationship between the data they collect and the AI, and how to use the AI‐based application effectively. They will be trained to interpret the prediction probabilities displayed by the AI and manage incorrect predictions. It is emphasized that the AI‐based application is a prototype, not a fully developed product, and that AI predictions may be incorrect and should not replace expert nursing judgment at this stage.

During wound care, the nurse will use a tablet or smartphone to take a picture of the wound and enter additional patient information, such as incontinence status, sensibility, and mobility. The AI checks the image's suitability for prediction based on exposure and definition. If the image quality is deemed inadequate, the system prompts the user to retake the image. The application does not request any personal patient information that would allow identification, such as name, date of birth, or case number. The AI‐based application automatically measures the wound using a patch as a reference point, and predicts the wound type, classification, and documentation characteristics based on the wound image and additional patient data. Additionally, the system displays the AI‐calculated probability for each characteristic. The nurse reviews and, if necessary, revises the AI's predictions to ensure accurate wound documentation and appropriate subsequent interventions. Optionally, the application suggests nursing interventions from the hospital's existing wound care standard operating procedures relevant to the documented wound type and characteristics. In additional information fields, the AI‐based application provides detailed descriptions and definitions of wound types (e.g., EPUAP and GLOBIAD classifications) and further information on in‐house wound management standards (e.g., contraindications or user instructions for specific wound dressings).

The primary difference between the standard documentation system and the AI‐based application is that photography and documentation are conducted on‐site using tablets and smartphones, unlike in standard care where documentation occurs post‐care using fixed PCs and digital cameras. Additionally, in the AI‐based application, the wound is automatically measured, and the wound type and characteristics are pre‐populated by the AI model based on the wound image, which then must be validated and revised by the nurse if necessary. In contrast, the standard systems only offer the option of using the last known values. Furthermore, the AI‐based application provides additional information such as wound severity categories and appropriate nursing interventions for the documented wound, features that are absent in the standard system.

By automatically measuring the wound and pre‐populating wound characteristics, the AI is expected to decrease the time required for wound documentation. Nevertheless, the decision‐making process regarding the documented wound characteristics and subsequent wound management remains with the nurse, who must critically review, confirm, or edit the characteristics as necessary. The use of the AI‐based application is not expected to lead to performance errors or adverse events, as all predictions are verified and, if necessary, corrected by the nurse.

### Measures

2.10

The measures of this study include the duration of wound assessment, dressing change, and documentation; the task load of the nurse during wound care and documentation; guideline adherence; and the accuracy of the AI predictions of wound type and classification in the clinical setting.

The duration of wound assessment, dressing change, and documentation is monitored during observation using standardized start and endpoints. The start point is defined as the moment dressing removal begins. If no dressing is present, the start point is the initiation of the first hands‐on wound care activity after patient positioning, such as a finger pressure test, measurement, or wound disinfection. Preparations, including patient positioning and material preparation, or interruptions, such as retrieving supplies from outside the room or responding to calls from other patients, are not included in the measurement. Documentation duration is measured separately since it does not always occur immediately after treatment. The start point is either opening the digital wound documentation or connecting the camera to the computer, and the endpoint is when the wound documentation is saved. It is also recorded whether a wound photograph is taken and whether the last known values are transferred from the existing documentation.

Guideline adherence is assessed using a set of five criteria identified during an expert workshop as relevant for evaluating guideline adherence in the context of wound care for PI and IAD. These criteria are derived from the “Prevention and Treatment of Pressure Ulcers” guideline published by the European Pressure Ulcer Advisory Panel (European Pressure Ulcer Advisory Panel, National Pressure Injury Advisory Panel, & Pan Pacific Pressure Injury Alliance 2019).

The selected criteria include performing a finger pressure test or the transparent disk method in the presence of redness (recommendation 9.1), accurately assessing wound type and classification (recommendation 9.2), applying wound edge protection in cases of macerated wound edges or surrounding skin (recommendation 3.1), and ensuring pressure relief for pressure injuries (recommendations 5.1 and 5.5). The response options for these criteria are binary: ‘No’ or ‘Yes or not required’. Sum scores are calculated from the responses, assigning a score of 1 to ‘Yes or not required’ and a score of 0 to ‘No’. Interrater reliability is also measured in the study. Additionally, the nurse's task load during wound assessment, dressing change, and documentation is evaluated using the standardized and validated NASA TLX questionnaire (Human Performance Research Group n.d.).

Other covariates measured include the nurse's professional experience, wound severity, and the general workload of the shift, which is assessed on a 5‐point scale relative to the average.

To assess the accuracy of the AI predictions of wound type and wound classification in the clinical setting, the wound is independently assessed on‐site by a member of the study team, separate from the nurse's assessment and the AI prediction. This assessment serves as the ground truth for calculating the accuracy of the AI predictions regarding wound type and classification.

Additionally, the usability of the documentation systems used, namely the standard clinical documentation systems and the AI‐based digital system, will be assessed in both the control and intervention groups. Usability will be evaluated using the two‐item UMUX Lite questionnaire with a 7‐point Likert scale (Lewis et al. 2013) because of its brevity (Borsci et al. 2020) and comparability with other studies and the SUS scale (Lewis et al. 2013).

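### The documentation clock covers different tasks in the two phases, so a separate regression on documentation duration does not compare like with like

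*Protocol article*

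**What the plan says.** Section 2.10 (Measures) defines two clocks.

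- **Care clock.** With a dressing in place, "The start point is defined as the moment dressing removal begins". Without one, it starts at the first hands-on activity, "such as a finger pressure test, measurement, or wound disinfection". Preparations and interruptions are excluded; the interruptions are described as "such as retrieving supplies from outside the room or responding to calls from other patients, are not included in the measurement". The article refers to standardized endpoints but does not spell out where this clock stops.
- **Documentation clock.** "Documentation duration is measured separately since it does not always occur immediately after treatment". The rule for starting it is: "The start point is either opening the digital wound documentation or connecting the camera to the computer". It stops when the nurse saves the record. Whether a photograph was taken is recorded.

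Section 2.8 (Standard Care) has nurses photograph with a digital camera and then upload at a computer. Section 2.9 (Intervention) places standard documentation after care, at a fixed PC. For the AI phase it says: "During wound care, the nurse will use a tablet or smartphone to take a picture of the wound and enter additional patient information". The application checks the image, asks for a retake if needed, and measures the wound from it. Section 2.5 confirms that the image is captured in the application.

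Section 2.12 plans one linear regression per dependent variable and lists assessment, dressing change and documentation. Section 2.6 lists a single time variable.

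**The concern.** Duration is the first-named outcome, and the hypothesis in section 2.1 is that the application shortens it. The documentation rule was written for a workflow in which documentation follows treatment. Section 2.9 then names bedside photography and documentation as the main difference between the two systems, and the timing rules do not address that difference.

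If the clock holds different tasks in the two phases, the AI coefficient in a documentation model mixes a real effect with relabelled time. Experience, severity and shift load cannot remove this, because the relabelling coincides with phase. It also touches the expected mechanism. Section 2.9 expects automatic measurement and pre-filled fields to cut documentation time, but manual measurement was never in the control documentation clock, so a saving on it cannot appear there.

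**Working it through.** **1. The plan's own figure.** Section 2.6 gives alpha 0.05, power 0.80, four predictors and a moderate effect. The article gives no number for that effect; f² = 0.15 is assumed here. Overall F test: noncentrality = 0.15 × 85 = 12.75 on 4 and 80 df, power 0.803. With 10% loss, 85 / 0.90 = 94.4, rounded up to 95. Both stated figures (85 and 95) reproduce. The present point does not change them.

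**2. Tasks against clocks.**

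| Task | Standard care | AI phase |
|---|---|---|
| Photograph | Camera, before connection to the PC: before the documentation clock | Taken in the open application: inside the documentation clock |
| Retake on poor image quality | No such prompt described | Inside the documentation clock |
| Measurement | Named as a hands-on activity that can start the care clock | Automatic, from the in-app image: inside the documentation clock |
| Patient data for the AI | Not described | Entered in the application during care: inside the documentation clock |
| Completing and saving the record | Inside the documentation clock | Inside the documentation clock |

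No camera is connected in the AI phase, so opening the application is the only start point that applies, and it must precede the photograph. The mismatch in the documentation clock therefore follows whether or not the care clock is paused.

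**3. Accounting with assumed minutes.** The article gives no task times. Assume equal true times in both phases: other care 10, photograph 1.5, measurement 1.5, entry 5. Assume also that the control photograph falls in the care clock.

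| | Care clock | Documentation clock | Sum |
|---|---|---|---|
| Control | 10 + 1.5 + 1.5 = 13 | 5 | 18 |
| AI, care clock paused during app use | 10 | 1.5 + 1.5 + 5 = 8 | 18 |
| AI, both clocks running | 10 + 8 = 18 | 8 | 26 |

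The true difference is zero. Documentation reads +3 against the AI under both rules. Care reads −3 (favouring the AI) if paused and +5 if not. The sum reads 0 if paused and +8 if not, the 8 overlapping minutes being counted twice.

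If the control photograph instead fell outside both clocks, the control sum would be 16.5, and even the paused AI sum of 18 would read +1.5 against the AI.

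**4. What such a shift does to the test.** Assume 42 and 43 nurses, 80 df, two-sided 0.05, and predictors uncorrelated with phase. The noncentrality of the AI coefficient is d / √(1/42 + 1/43) = d / 0.217, where d is the shift in residual SDs.

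| Shift d | Chance of a significant AI coefficient, no true effect | Power, true saving of 2√0.15 = 0.77 SD, shift opposing it |
|---|---|---|
| 0 | 0.05 | 0.94 |
| 0.2 | 0.15 | 0.74 |
| 0.4 | 0.45 | 0.40 |
| 0.6 | 0.78 | 0.13 |

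In minutes, a shift of 1 gives a false-positive chance of 0.33, 0.15 or 0.09 for an assumed SD of 3, 5 or 8. A shift of 3 gives 0.995, 0.78 or 0.40.

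**The case against.** **The overlap is inferred.** No sentence says that both clocks run together. Timing documentation separately could mean its minutes are kept out of the care clock, and a pause rule is the kind of detail a journal article leaves to the observation form or full protocol, neither of which is shown. This stands. Section 2.3 says AI-phase observations follow the pre-intervention procedures, and the Discussion reports no change of method. Neither statement points to a phase-specific rule, but neither excludes one.

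**The same minutes cannot both move between clocks and be counted twice.** This stands too. If the care clock pauses, photography has moved and the sum is fair. If it does not pause, photography is in both clocks and the sum is inflated. These are alternatives.

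**The outcome may already be a total.** Section 2.6 supports that reading, and a sum of non-overlapping clocks would be comparable provided control photography was timed. Section 2.12 leaves it unsettled.

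**The control photograph is not stated to fall in the care clock.** Correct. A dressed wound has to be uncovered to be photographed, which makes it likely, but no end of that clock is given. The documentation mismatch does not need this premise, because the photograph precedes connecting the camera in any case.

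**Bedside work is part of the intervention.** Yes, and a total captures that change fairly. The problem is only how the work is allocated to clocks.

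**The study is an exploratory pilot.** That bears on multiplicity. It does not make an outcome timed differently in the two groups comparable.

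**Conclusion.** The point holds for documentation duration: under the stated rule the clock contains photography and measurement in the AI phase and not in standard care. A separate regression on it is confounded with phase by construction. The care-duration comparison may be mismatched as well, depending on the unstated pause rule and on where control photography fell.

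A reader might go further and infer that every planned duration comparison is biased by definition, that minutes are certainly double counted, or that the error has a known direction. The article does not support this. A sum of non-overlapping clocks would be fair, the overlap is an inference, and the direction depends on the clock and the pause rule: the documentation clock leans against the AI, a paused care clock leans towards it. Every minute, SD and effect size in the illustrations is assumed. They show that a shift of a few minutes could matter at 85 nurses, not that one of that size occurred. The sample size is unaffected.

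**What to change.** 1. In sections 2.10 and 2.12, make total hands-on time for care plus documentation the main duration outcome, excluding interruptions and idle gaps and counting each minute once. Include photography and measurement in the total in both phases.
2. Report the care and documentation components descriptively only.
3. State the start, stop and pause rules of each clock in each phase, in particular whether the care clock is paused during app use. If it is not, record overlap minutes for the remaining AI-phase observations.
4. For AI-phase cases already observed with unrecorded overlap, run a bounding sensitivity analysis. Total = care + documentation − overlap, so it lies between the longer of the two clocks and their sum. In the overlapping illustration (18 and 8) the bounds are 18 and 26.

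The cost is a change of definition and one extra field. The total needs no split of photo minutes in the completed control group, provided its two clocks between them captured the photography. Control photography that fell outside both clocks cannot be re-timed and should be stated as a limitation. The bounds will be wide where many AI-phase cases lack overlap data, and the later the field is added, the more such cases there will be.

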### Sample Size

2.6

Based on current methodologies, we performed an a priori sample size calculation using power analysis (Döring and Bortz 2016) with the G*Power 3 software (Faul et al. 2007). For this calculation, we assumed moderate effect sizes between dependent and independent variables (Cohen 1988), an alpha level of 0.05, and a power of 0.80. To test correlations between dependent variables (task load, time, guideline adherence) and four independent variables (use of the demonstrator, general load of the shift, professional experience, severity of wound) using multivariate models (multiple linear regression) under these assumptions, we will require a total of 85 nurses.

With a calculated sample size of 85 nurses and considering up to four independent variables, we anticipate obtaining meaningful results within a manageable timeframe and with the available resources. Accounting for a projected 10% dropout and missing rate, based on experiences from previous studies, we plan to recruit 95 nurses to ensure a sufficiently large sample for subsequent evaluation.

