### Analysis Plan

2.12

Once data collection is complete, we will use multiple linear regression models to examine the effects of the AI‐based digital system on the duration of wound assessment, dressing change, documentation, perceived task load, and guideline adherence. We will calculate an individual linear regression model for each dependent variable and incorporate potential covariates such as the nurses’ professional experience, wound severity, and the general load of the shift. Nominal and ordinal variables (use of the AI demonstrator, severity of the wound, general burden of the shift, and guideline adherence) will be dummy coded. We will then assess each model for linearity, homoscedasticity, and the absence of multicollinearity to satisfy the assumptions of linear regression. If these conditions are met, we will proceed with standard multiple linear regression, incorporating all independent variables as predictors. The f‐test will be used to examine the extent to which the independent variables predict the dependent variable, with R² indicating how much of the variance in the dependent variable can be explained by the independent variables. The t‐test will assess the significance of the predictors. To determine the specific contribution of the use of the demonstrator, we will calculate the explanatory power for both the full regression model and a reduced model without the demonstrator use variable, using the difference in explanatory performance to isolate the effect attributable to the demonstrator use. Datasets with missing socio‐demographic data for nurses, used only to describe the sample and not part of the statistical analysis, will still be included in the analysis. However, datasets with missing values for independent variables will be excluded entirely, and datasets with missing values for dependent variables will be excluded only from the specific model where the data is missing. The significance level is set at 0.05. As this is an exploratory study and a separate model is calculated for each dependent variable, no correction for alpha error is required. To analyze the interrater reliability of the observers, we will use Kendall's rank correlation coefficient (Kendall's tau). To determine the performance of the AI‐based application in the clinical setting, we will calculate its accuracy in predicting wound type and wound classification, using the on‐site assessment of a study team member as ground truth. Additionally, we will descriptively evaluate the usability of both the standard clinical documentation systems and the AI‐based application in terms of central tendency, variability, and distribution.

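### The adherence score gives IAD wounds the pressure-relief credit automatically, and wound type is not a named covariate, so a change in PI/IAD mix between phases would bias the AI coefficient in either direction

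*Protocol article*

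**What the plan says.** All references are to the protocol article.

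- **Number of items.** Measures says "Guideline adherence is assessed using a set of five criteria identified during an expert workshop", so the score runs from 0 to 5. The list that follows has four entries, the last citing two recommendations. The text does not say how the entries make up five items, so pressure relief may count once or twice.
- **Response format.** "The response options for these criteria are binary: ‘No’ or ‘Yes or not required". Done and not applicable share one category.
- **Scoring.** "Sum scores are calculated from the responses, assigning a score of 1 to ‘Yes or not required’ and a score of 0 to ‘No".
- **Conditional criteria.** One is tied to wound type: "ensuring pressure relief for pressure injuries (recommendations 5.1 and 5.5". Two are tied to how the wound presents: "performing a finger pressure test or the transparent disk method in the presence of redness (recommendation 9.1" and "applying wound edge protection in cases of macerated wound edges or surrounding skin (recommendation 3.1".
- **Model.** Sample Size names "four independent variables (use of the demonstrator, general load of the shift, professional experience, severity of wound". The Analysis Plan will "incorporate potential covariates such as the nurses’ professional experience, wound severity, and the general load of the shift". Neither names wound type, and the article does not define wound severity.
- **Design.** Design and Discussion describe consecutive, non-randomized groups. Control data were collected from May 2023 to January 2024, and intervention data from July 2024. No matching or stratification by wound type is described.

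**The concern.** A sum score of this kind should move only when nurses act differently. Here it also moves when the wounds differ. For a PI, the pressure-relief point depends on what the nurse does. For an IAD wound, the point is given.

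With randomized groups, this would mostly add noise. With two consecutive periods some months apart, on eight wards of different kinds, the PI/IAD mix can differ by chance or by season, and nothing named in the model is certain to absorb the difference. More IAD in the AI phase would look like better adherence, and more PI would look like worse adherence. Adherence is one of the three outcomes in the study hypothesis, so a case-mix difference could be reported as an effect of the application.

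**Working it through.** **The plan's own figure first.** The article requires 85 nurses for a regression with four predictors, alpha 0.05, power 0.80 and a moderate effect. Taking moderate as f² = 0.15 (not printed, so an assumption), the overall F test with 4 and N − 5 degrees of freedom and noncentrality 0.15 × N has power 0.797 at N = 84 and 0.803 at N = 85. The 85 reproduces, and 85 / 0.90 = 94.4 gives the 95 to recruit. Neither figure is disputed; N = 85 is used below.

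**Inputs that the article does not give (assumed).** Adherence to pressure relief in PI, p = 0.60. Adherence on all other items, 0.75. No AI effect. Groups of 43 and 42. Severity unrelated to wound type. Number of relief items, m = 1 or 2. Fall in PI share from control to AI phase, d = 0.10, 0.20 or 0.40.

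**Bias.** An IAD wound scores m on the relief items and a PI scores m × p on average. The spurious difference in mean score is therefore d × (1 − p) × m.

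**False-positive rate.** Simulated trials, with the score regressed on AI use, experience, shift load and severity, tested at 5%.

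| Fall in PI share | Bias, one item | False positives | Bias, two items | False positives |
|---|---|---|---|---|
| 10 points | 0.1 × 0.4 × 1 = 0.04 | about 5% | 0.1 × 0.4 × 2 = 0.08 | about 6% |
| 20 points | 0.2 × 0.4 × 1 = 0.08 | 7% | 0.2 × 0.4 × 2 = 0.16 | 11% |
| 40 points | 0.4 × 0.4 × 1 = 0.16 | 12% | 0.4 × 0.4 × 2 = 0.32 | 29% |

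Repeat runs move the larger entries by one or two percentage points. A rise in PI share gives the same sizes with a negative sign.

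**Hand check of one entry.** With a score SD of about 1.0, the standard error is 1.0 × √(1/43 + 1/42) = 0.217. For a bias of 0.16, the ratio is 0.16 / 0.217 = 0.74. The chance of passing ±1.99 is P(Z > 1.25) + P(Z < −2.73) = 0.106 + 0.003, about 11%.

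**Other adherence levels.** At 80% relief adherence in PI, a 20-point shift gives 5.9% (one item) or 7.5% (two). With relief adherence at 50% and the other items at 80%, it gives 8.9% or 15.4%.

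**Does a remedy remove it?**
- Wound type as a covariate: AI coefficient within about 0.005 of zero and false positives of 4.6–5.4% in every setting tried.
- Scoring only applicable items as a proportion, without the covariate: usually 5–11%, and up to 22% in the most extreme setting (two relief items, 30% relief adherence in PI against 80% elsewhere, IAD share rising from 30% to 60%). Bias remains because PI and IAD are then scored on different sets of items.

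**The case against.** The strongest objection is that severity may already do the work. The only classification systems that the article names are specific to one wound type: EPUAP for PI and GLOBIAD for IAD. The Analysis Plan dummy-codes severity. If the dummies are those categories, they identify wound type. Simulation with such dummies gave false positives of 4.7–5.8% and bias of at most 0.01 points. This stands as a possibility, but the article does not define severity. If severity is merely correlated with type (1 SD apart), only part of the bias goes: in one two-item setting the false-positive rate fell from 27.2% to 20.4%.

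Second, no shift in mix is documented. Both phases use the same wards and eligibility rules, and no change in wound-care processes is expected. This stands too: the point is a risk, and for a 10-point shift a negligible one.

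Third, this is an exploratory pilot whose Discussion concedes slight bias from consecutive groups and says that only the most important factors were modelled. That lowers the stakes. The Discussion names ward affiliation as omitted, but not wound type, which is built into the score itself.

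A reader might also infer more than the text supports:
- *All three conditional criteria depend on wound type.* Only pressure relief is stated that way. The article does not link redness or maceration to PI versus IAD.
- *The study will overstate the AI's benefit.* The direction follows the mix and could equally suggest harm.
- *Automatic points will push scores to the ceiling and hide a real effect.* This is plausible, but the article gives no adherence rates from which to show it.

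**Conclusion.** The point holds as a conditional bias that is cheap to prevent. From the text alone, at least one of the five items is met automatically by IAD wounds, the groups are non-randomized and consecutive, and wound type is not a named covariate.

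The size depends on unreported quantities. Under the assumptions above, it is close to nominal for a 10-point change in PI share, modest at 20 points, and serious at 40 points only if relief counts as two items. Higher relief adherence in PI shrinks it. Type-specific severity coding would all but remove it. The article does not show that the mix changed, so it does not support saying that the adherence result will be wrong. It supports saying that the named model is not certain to separate the AI effect from a change in mix. The adherence model should be amended before analysis.

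**What to change.** 1. **Main change.** Add wound type (PI or IAD) as a covariate in the adherence model, taken from the study team's on-site assessment in both phases and not from the nurse's or the AI's label. Alternatively, state that severity is coded in type-specific EPUAP and GLOBIAD categories, which serves the same purpose.
2. **Reporting.** Give the PI/IAD mix in each phase, and say how the five items are made up.
3. **Sensitivity analysis.** Rescore pressure relief only where it applies, using the on-site wound type in the same way in both phases. Proportion scoring should not replace the covariate, because it can leave bias.
4. **What to avoid.** Do not split the response options on the form now. Control collection closed in January 2024, so the instrument would differ between phases.

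**Cost.** One degree of freedom, and a slightly wider interval if the mix did shift. With equal groups averaging 60% PI, the squared correlation between wound type and phase is (0.2 × 0.5)² / (0.6 × 0.4) = 0.042 for a 20-point shift. The standard error then grows by √(1 / 0.958) − 1, about 2%. No new data should be needed: the criterion on correct wound type already requires a reference in both phases, and Data Collection and Management lists on-site wound assessments among the study team's tasks. The team should confirm that wound type was recorded for every control case.
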